### Ethics Approval

This study protocol was approved by the institutional review board (IRB) at Sapporo Medical University Hospital (approval number: 29-15). Changes to the protocol will require IRB and Japanese PMDA approval. The trial will be conducted in accordance with the ethical principles of the Declaration of Helsinki, the Japanese Pharmaceutical Affairs Law, and good clinical practice. Trial investigators will obtain written informed consent from each participant before study inclusion. If the participants do not have the ability to write, written informed consent will be obtained from a legal representative alone. Participants will be free to withdraw from the study at any time.

### Consent for Publication

The results from our study will be presented in peer-reviewed publications and meetings without identifying data. Written consent for publication will be obtained from all participants in the study.

### Eligibility Criteria

Since MSCs will be collected from the participants (autologous MSCs) in our study, we must start the MSC cultures after primary registration in order to initiate the collection of peripheral blood and bone marrow when the protocol therapy starts. Afterward, we must confirm that the MSC product passed the shipping standards before infusion. Thus, we must perform a secondary registration of the participants. Therefore, case registration will require 2 steps in the trial; we will register the participants before blood and bone marrow collections (first registration) and before the infusion of MSCs (second registration).

### Inclusion Criteria at the Time of the First Registration

For the first registration, the inclusion criteria will be as follows: (1) a brain injury oth.er than stroke diagnosed via magnetic resonance imaging (MRI), computed tomography, 3D computed tomography angiography (3D-CTA), or angiography (including a suspected brain injury other than stroke); (2) a classification of grade 3 to 5 on the mRS; (3) patients aged 20 to 80 years; (4) patients whose rehabilitation can be performed for at least 80 minutes per weekday; and (5) written informed consent, which will be obtained as much as possible from the participants. If a participant does not have ability to write, written informed consent will be obtained from a legal representative alone.

### Exclusion Criteria at the Time of the First Registration

For the first registration, the exclusion criteria will be as follows:

Severe disturbance of consciousness (a Japan Coma Scale score of between 200 and 300)Severe contracture, deformity, or calcification of a jointDiagnosed with hepatitis B, hepatitis C, or syphilis via initial screeningPancytopenia (a white blood cell concentration of <2000 cells/µL, hemoglobin concentration of <10.0 g/dl, or platelet concentration of <100,000 platelets/µL)MRI (or computed tomography) scan revealing a severe asymptomatic lesion or white matter lesionMRI scan revealing multiple and severe instances of microbleeding or hemosiderosis in the whole brainHead and neck magnetic resonance angiography (or 3D-CTA or angiography) scan revealing ≥70% stenosis of main cerebral arteries and cervical carotid arteries even after the revascularization (except for complete occlusion) or dissection of an arteryHead and neck magnetic resonance angiography (or 3D-CTA or angiography) scan revealing severe arteriosclerotic change or severe calcificationMoyamoya disease, cerebral aneurysm, and other vascular malformations with a high risk of rupture or cerebral embolismUncontrollable hypertension with therapy prior to infusion (systolic pressure: >140 mm Hg; diastolic pressure: >90 mm Hg)Past history of neoplasms (except complete response); severe diseases of the blood and blood-forming organs; certain disorders involving the immune mechanism; severe mental and behavioral disorders; severe diseases of the nervous system; and severe congenital malformations, deformations, and chromosomal abnormalitiesPast history of penicillin and streptomycin allergy or other severe allergy (shock or anaphylactic symptoms)Poor general condition due to endocrine, nutritional, and metabolic diseases; uncontrollable mental disorders; diseases of the nervous system (refractory epilepsy), diseases of the circulatory system (uncontrollable and refractory heart failure, moderate or severe valvular heart disorder, uncontrollable and refractory atrial fibrillation, refractory atrial and ventricular thrombi, a history of ischemic heart disease with percutaneous coronary intervention within the past 12 months, and serious arrhythmia); diseases of the respiratory system; diseases of the digestive system; diseases of the musculoskeletal system and connective tissue; diseases of the genitourinary system (dialysis); injury; poisoning; and certain other consequences of external causesParticipation in another clinical trial related to any organ or a past history of cellular therapyPregnant or possibly pregnant women, nursing women, women who plan to be pregnant during the study period, or male patients who want their partners to get pregnantOther patients who are judged by investigators holding a medical license as inappropriate for the study

### Inclusion Criteria at the Time of the Second Registration

For the second registration, the inclusion criteria will be as follows: (1) ≥180 days after the onset of a brain injury other than stroke; (2) patients who, after rehabilitation for at least 80 minutes per weekday or as much as possible over the past 1 month or more, showed no improvement in FMA score over the last 2 weeks (definition of *improvement in FMA score*: improvement by 1 point or more, as shown by the total FMA score); (3) a classification of grade 3 to 5 on the mRS; and (4) patients who are ready for the infusion of STR-01 that satisfies the specifications of the acceptance criteria.

### Exclusion Criteria at the Time of the Second Registration

For the second registration, the exclusion criteria will be as follows:

Severe disturbance of consciousness (Japan Coma Scale score of between 200 and 300)Diagnosed with hepatitis B, hepatitis C, HIV, human T-lymphotropic virus 1 infection, syphilis, or human parvovirus B19 infection via detailed examinationMore than 70% stenosis of main cerebral arteries and cervical carotid and vertebral arteries even after the revascularization (except for complete occlusion and a healed dissecting artery) or dissection of an arterySevere arteriosclerotic change and calcificationMoyamoya disease, cerebral aneurysm, or other vascular malformations with a high risk of rupture or cerebral embolismUncontrollable hypertension with therapy prior to infusionIschemic heart disease (more than 75% stenosis of coronary arteries)Cardiac shunt malformation (ventricular septal defect or arterial septal defect)Possible large thrombus, as determined via laboratory examinationNeoplasms (except complete response); severe diseases of the blood and blood-forming organs; certain disorders involving the immune mechanism; severe mental and behavioral disorders; severe diseases of the nervous system; and severe congenital malformations, deformations, and chromosomal abnormalitiesPenicillin and streptomycin allergy and other severe allergy (shock or anaphylactic symptoms)Poor general condition due to endocrine, nutritional, and metabolic diseases; uncontrollable mental disorders; diseases of the nervous system (refractory epilepsy), diseases of the circulatory system (uncontrollable and refractory heart failure, moderate or severe valvular heart disorder, uncontrollable and refractory atrial fibrillation, refractory atrial and ventricular thrombi, a history of ischemic heart disease and percutaneous coronary intervention within the past 12 months, and serious arrhythmia); diseases of the respiratory system; diseases of the digestive system; diseases of the musculoskeletal system and connective tissue; diseases of the genitourinary system (dialysis); injury; poisoning; and certain other consequences of external causesPregnant women, nursing women, those who plan to be pregnant during the study period, or male patients who want their partners to get pregnantOther patients who are judged by investigators holding a medical license as inappropriate for the study

### Outcome Measures

Outcome measures will be performed by more than 2 Japanese board-certified neurosurgeons at Sapporo Medical University Hospital**.**

#### Primary Outcome

The primary outcome is the proportion of cases in which the mRS grade improves by 1 point or more between 180 (±14) days after the injection of STR-01 and just before injection (−14 to 0 days).

#### Secondary Outcomes

The following are the secondary outcomes: (1) the rate of all adverse events during the whole study period, (2) the differences in FMA scores (each item score and total score) between 180 (±14) days after the injection of STR-01 and just before injection (−14 to 0 days), (3) the differences in National Institutes of Health Stroke Scale scores (each item score and total score) between 180 (±14) days after the injection of STR-01 and just before injection (−14 to 0 days), and (4) the differences in Functional Independence Measure scores (each item score and total score) between 180 (±14) days after the injection of STR-01 and just before injection (−14 to 0 days).

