### Sample Size

We will recruit 10 people (minimum: 6; maximum: 20) with a modified Rankin Scale (mRS) grade of 3 to 5. The focus of our trial is to establish safety and potential efficacy. However, it should be noted that if the proportion of cases in which the mRS grade improves by 1 point or more exceeds 10%, the trial will provide significant clinical benefit. To detect a difference by using a *Z*-test with continuity correction, a minimum of 6 people is required. Thus, the target sample size of people with an mRS grade of 3 to 5 was determined to be 10 (minimum: 6; maximum: 10), under the consideration of dropout.

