#### Secondary Outcome Measure

We will estimate the proportion of cases with at least 1 level of improvement in mRS grade and the 95% CI by using the scoring method at 180 (±14) days after MSC infusion. We will also estimate the mean changes in FMA, National Institutes of Health Stroke Scale, and Functional Independence Measure scores from immediately before (−14 to 0 days) MSC infusion to 180 (±14) days after MSC infusion and the 95% CIs by using the Wald method.

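### Every item of the FMA, NIHSS and FIM ranks as a secondary outcome, and a 95% Wald interval for an item's mean change is unreliable at about 10 patients when few patients change on it

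*Protocol article*

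**What the plan says.** The Secondary Outcomes section of the protocol article lists "the differences in FMA scores (each item score and total score", then "the differences in National Institutes of Health Stroke Scale scores (each item score and total score" and "the differences in Functional Independence Measure scores (each item score and total score". All are measured from just before infusion to day 180. No total is placed above its items.

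The Secondary Outcome Measure section, under Statistical Analysis, covers "mean changes in FMA, National Institutes of Health Stroke Scale, and Functional Independence Measure scores" and adds "the 95% CIs by using the Wald method". It does not mention items separately and gives no other analysis for them.

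The Sample Size section opens with "We will recruit 10 people (minimum: 6; maximum: 20" and closes with a target that "was determined to be 10 (minimum: 6; maximum: 10". The target is therefore 10 and the minimum 6, while the maximum is given as both 20 and 10.

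**The concern.** A Wald interval takes its width from the sample standard deviation. If an item has few levels and nobody in a small sample changes on it, the standard deviation is zero and the 95% interval becomes the single point zero. It looks like precise evidence of no change, but it shows only that a few patients did not move. If an item moves more often, the normal multiplier is too small for 6 to 10 patients, and the lower limit can pass zero by chance more often than it should.

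With items and totals ranked alike, both kinds of interval would stand beside the three totals in the report of an open-label, single-arm trial. The Discussion says the data will feed the protocol of a later, larger trial, so misleading item intervals could influence that step.

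**Working it through.** **Plan's own figure.** None is stated for the secondary intervals. The minimum of 6 belongs to the primary Z-test and plays no part here.

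**Inputs.** From the article: n=6 and n=10, n=20 if the larger maximum applies, and a 95% Wald interval. Assumed, because the article gives neither: each item's change is +1, 0 or -1 (positive = better) with probabilities p+, 1 - p+ - p-, and p-; and the number of items is 30 to 100.

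**Formula.** With *a* patients gaining and *b* losing: mean m = (a - b)/n, variance s² = (a + b - n·m²)/(n - 1), interval m ± 1.96·s/√n. All (a, b) are enumerated with their multinomial probabilities.

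**Step 1: zero width when nobody changes.** With change probability q per patient, P(nobody changes) = (1 - q)^n.
- q = 10%: 0.9^6 = 53%, 0.9^10 = 35%, 0.9^20 = 12%.
- q = 20%: 26%, 11%, 1%.
- This exceeds one half only if q < 1 - 0.5^(1/n): 10.9% (n=6), 6.7% (n=10), 3.4% (n=20).

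**Step 2: coverage under a true gain.** Example with n=10, p+ = 10%, p- = 0, so the true mean change is 0.1:
- a = 0 gives [0, 0], which misses 0.1 (probability 0.349).
- a = 1 to 4 gives intervals that contain 0.1. For instance, a = 4 has s = 0.516 and 0.4 ± 0.320 = [0.080, 0.720].
- a ≥ 5 gives intervals lying wholly above 0.1 (probability 0.002).
- Coverage = 1 - 0.349 - 0.002 = 0.65.

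| True gain, none losing | n=6 | n=10 | n=20 |
|---|---|---|---|
| 5% | 26% | 40% | 64% |
| 10% | 47% | 65% | 88% |
| 20% | 72% | 89% | 92% |

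With the t multiplier, coverage at the 10% gain rate is again 47%, 65% and 88%, because any multiple of s = 0 is 0.

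**Step 3: no true mean change (p+ = p-).** For total change rates of 2% to 60%, coverage is 87-100% (n=6), 89-100% (n=10) and 93-100% (n=20). A collapsed interval at zero then contains the truth. The chance that the lower limit exceeds zero (nominal 2.5%) is:

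| Patients changing | n=6 | n=10 |
|---|---|---|
| 5% | 0.03% | 0.14% |
| 10% | 0.2% | 0.8% |
| 20% to 50% | 1.1% to 5.8% | 3.2% to 5.4% |

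Here the t multiplier does help: at 20% to 40% changing it gives 0.1-1.0% (n=6) and 0.6-2.4% (n=10).

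**Step 4: scale of the chance findings.** Expected falsely improved items = number of items × rate. At n=10 with an assumed 50 items, this is 50 × 0.8% = 0.4 at a 10% change rate and 50 × 3.2% = 1.6 at 20%. For 30 to 100 items the ranges are 0.2 to 0.8 and about 1 to 3.2.

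**The case against.** Four points can fairly be made against this.

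- **The item interval is inferred.** The analysis section speaks of scores on the three scales without repeating that each item is meant, and refers to an analysis plan that is not shown for detail. This stands as a caution. But the outcome list defines those scores as item and total, and the interval method is stated, so the inference is the natural one. The point concerns a stated rule and not an omission.
- **A reader might infer that most item intervals will collapse or cover far below 95%.** The documents do not support that. It needs change rates below 10.9%, 6.7% or 3.4% at n=6, 10 or 20, and no item change rates are given. With no true mean change, coverage is mostly close to nominal or above it.
- **A reader might also infer that one report will be full of zero-width intervals and of falsely improved items.** The two problems need different change rates. At 10% changing or less, chance improvement is under 1% per item; at 20% or more, collapse is uncommon except at n=6 (26% at a 20% rate). A mix of items could show some of each, but the problems mainly affect different items.
- **No test, success rule or claim is tied to any item.** The article has one primary outcome, and unadjusted secondary estimates are ordinary in a small phase 2 trial. So the chance-improvement point concerns interpretation and is not a breach of error control.

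None of this rescues an interval that covers 65% at the target sample size when a small true gain exists.

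**Conclusion.** The point holds in a limited form, and its severity is minor. For coarse items on which few patients change, the stated interval is not a 95% interval at the planned size. With a 10% true gain and no losses it covers 47% (n=6), 65% (n=10) and 88% (n=20), mostly because it shrinks to zero width, and changing to a t interval leaves that untouched. For items that change more often with no net gain, false improvement at n=10 is up to about twice nominal (5.4% against 2.5%).

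This rests on item changes of one point at most, on assumed change rates, and on reading the outcome list and the analysis section together. The number of items affects only the expected counts of chance findings. The n=20 figures apply only if the larger of the two stated maxima is the intended one.

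**What to change.** In Secondary Outcomes, name the total FMA, NIHSS and FIM scores as the secondary efficacy outcomes. In Secondary Outcome Measure, limit interval estimates to those three totals. Report each item as the number of patients improved, unchanged and worsened, with no item-level interval and no efficacy statement resting on a single item. Carry the same wording into the analysis plan.

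The totals are much less exposed. If their changes are roughly normal, the Wald interval covers 89.3% (n=6), 91.8% (n=10) and 93.5% (n=20), and a t interval restores 95%.

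The cost is a change of wording and no new data. The downside is that item results become descriptive only.

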### Statistical Analysis

The plan of analysis for study data will be performed by a biomedical statistician ([name]), and statistical analyses will be performed by using JMP 11.1 for Windows (SAS Institute Inc). The details are described in our statistical analysis plan and are described briefly in the following subsections.

#### Primary Outcome Measure

The valid target population is patients with an mRS grade of 3 to 5 before MSC infusion. We assume that the proportion of cases without MSC infusion in which the mRS grade improves by 1 point or more will be 0.1%. We will perform a Z-test with continuity correction at 180 (±14) days after MSC infusion.

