**Figure 1 figure1:**
[figure not shown]
Clinical protocol. FMA: Fugl-Meyer assessment; MSC: mesenchymal stem cell.

We propose to provide an extensive rehabilitation protocol to all participants prior to MSC infusion in order to exclude the potential effects of rehabilitation alone and evaluate MSC-specific effects. Briefly, all patients with chronic brain injury will receive formal rehabilitation (at least 80 min/weekday for 4 weeks) and continue formal rehabilitation until they show no further improvements in Fugl-Meyer assessment (FMA) scores for the last 2 weeks prior to MSC infusion. Thus, we expect to evaluate the therapeutic effects of MSC infusion in addition to the effects of rehabilitation therapy. We will evaluate FMA scores approximately every week. The clinical data will be collected by at least 1 physical therapist and at least 1 Japanese board-certified neurosurgeon at Sapporo Medical University Hospital. If the patients require more than 2 weeks to reach an FMA score plateau, we will continue formal rehabilitation until they show no further improvements for the next 2 weeks.

For cell preparation, peripheral blood draws from each patient for autoserum and bone marrow collection will be performed. The autologous MSCs will be cultured in autologous sera, and the autologous human MSCs (called *STR-01*) will be manufactured in a cell processing center at Sapporo Medical University. STR-01 will be prepared under good manufacturing practice conditions by personnel, who have received formal good manufacturing practice training, within a facility with highly controlled temperature, room air, pressure, and environmental conditions and then cryopreserved at −150 °C until its use, as previously described [28]. On the day of infusion, cryopreserved units will be thawed at the bedside in a 37 °C water bath and will be administered with saline to each patient for approximately 60 minutes. The total number of cells in the STR-01 product is based on our previous study (0.5 × 10^8^ to 2 × 10^8^ cells per patient) [27]. Hospital treatment, including rehabilitation for a target of 80 min/weekday, will be performed for 180 (±14) post-MSC infusion days, after which final outcome measures will be evaluated.

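### The primary test is set against 0.1%, so one improved patient makes it significant at any planned sample size without showing the benefit rate above 10% that the protocol names

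*Protocol article*

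**What the plan says.** All references are to the protocol article.

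- Outcome Measures, Primary Outcome: "The primary outcome is the proportion of cases in which the mRS grade improves by 1 point or more", comparing day 180 (±14) with the assessment just before injection.
- Statistical Analysis, Primary Outcome Measure: "We assume that the proportion of cases without MSC infusion in which the mRS grade improves by 1 point or more will be 0.1", with the figure printed as a percentage, 0.1%. The next sentence is "We will perform a Z-test with continuity correction at 180 (±14) days after MSC infusion". The 0.1% is therefore the reference value of the primary test.
- Sample Size: "if the proportion of cases in which the mRS grade improves by 1 point or more exceeds 10%, the trial will provide significant clinical benefit". The same section says that for this test "a minimum of 6 people is required".
- Sample Size also states "We will recruit 10 people (minimum: 6; maximum: 20) with a modified Rankin Scale (mRS) grade of 3 to 5" and later gives a maximum of 10. The Abstract gives 6 to 20.
- Study Design describes a single-arm, open-label trial. The text after Figure 1 adds: "Hospital treatment, including rehabilitation for a target of 80 min/weekday, will be performed for 180 (±14) post-MSC infusion days".

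The article gives no alpha, sidedness or power, and no source for the 0.1%.

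**The concern.** The value tested and the value linked to benefit concern the same endpoint and differ 100-fold. With a reference of 1 in 1000 and at most 20 patients, the expected number of responders under the null is at most 0.02, so one responder is bound to be extreme. The test then asks only whether anyone improved by a grade. That is a weak question where grading is open label, there is no control group, and rehabilitation runs through the whole follow-up. The Discussion says that signs of efficacy, with safety, could lead to a larger controlled trial, so how a significant result is read matters.

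**Working it through.** **Inputs.** Reference rate p0 = 0.001 (Primary Outcome Measure); benefit threshold 10% (Sample Size); n = 6, 10 and 20 (Sample Size, Abstract). Assumed: alpha 0.05, checked one- and two-sided.

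**1. The plan's own minimum of 6.** It cannot be pinned down without alpha, power and an alternative. The formula is n0 = [(z_alpha·√(p0q0) + z_power·√(p1q1))/(p1−p0)]², then n = (n0/4)·[1 + √(1 + 2/(n0·|p1−p0|))]² with continuity correction.

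- 0.1% vs 10%, 80% power: n = 19, one- or two-sided. At 50% power, n = 7.
- 0.1% vs 30%, two-sided 0.05, 80% power: n = 6 (5.03 before rounding up).
- 10% vs 60%, two-sided 0.05, 80% power: n = 6 (5.83 before rounding up).

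A minimum of 6 fits either a 0.1% or a 10% null, so it does not tell us which was meant.

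**2. One responder against 0.1%.** z = (x − n·p0 − 0.5)/√(n·p0·(1−p0)) with x = 1. The exact one-sided p is 1 − 0.999ⁿ.

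| n | z | exact p |
|---|---|---|
| 6 | 0.494/0.0774 = 6.38 | 0.006 |
| 10 | 0.490/0.0999 = 4.90 | 0.010 |
| 20 | 0.480/0.1414 = 3.40 | 0.020 |

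z falls as n rises, so every size from 6 to 20 lies within these limits. The conflicting maxima (20 and 10) make no difference. The observed proportions are 1/10 = 10%, which does not exceed 10%, and 1/20 = 5%, which is below it.

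**3. Chance of a significant result.** The rule is at least one responder, so P = 1 − (1−p)ⁿ.

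| true rate p | n = 6 | n = 10 | n = 20 |
|---|---|---|---|
| 1% | 6% | 10% | 18% |
| 2% | 11% | 18% | 33% |
| 5% | 26% | 40% | 64% |
| 10% | 47% | 65% | 88% |

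The rates of 1%, 2% and 5% without cells are assumptions that show the sensitivity; the article gives no such figures. At n = 10 the rule keeps its error at 2.5% only if the true rate is below 1 − 0.975^(1/10) = 0.25%.

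**4. What is needed to support a rate above 10%.** The smallest count whose exact (Clopper-Pearson) 95% lower limit exceeds 10%, with its exact tail at a true 10%:

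| n | count | lower limit | tail at 10% |
|---|---|---|---|
| 6 | 3 | 11.8% | 1.6% |
| 10 | 4 | 12.2% | 1.3% |
| 20 | 6 | 11.9% | 1.1% |

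The score interval planned under Secondary Outcome Measure is looser. At 3/10 its lower limit is already 10.8%, while the exact tail P(X ≥ 3) at a true 10% is 7.0%.

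**5. Chance of meeting the exact rule.**

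| true rate | n = 6 | n = 10 |
|---|---|---|
| 30% | 26% | 35% |
| 40% | 46% | 62% |
| 50% | 66% | 83% |

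**The case against.** The best defence is that 0.1% is the assumed untreated rate and 10% the worthwhile rate. Pairing such a null with such a target is ordinary design. This stands: the Sample Size sentence makes a rate above 10% sufficient for benefit and does not set it as the null or as a required success rule. A reader might infer that the two figures flatly contradict each other, or that the test must use 10%; the text supports neither. Even so, rejecting the lower figure does not show that the higher one is exceeded.

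Second, the run-in is meant to remove rehabilitation effects: patients are at least 180 days from onset and show no Fugl-Meyer gain over the last two weeks. That is a reason to expect a low rate. But two flat weeks on one scale do not establish 1 in 1000 on another scale over 180 further days of rehabilitation. A source for 0.1% may stand in the full protocol; the one-responder result does not depend on it.

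Third, the article already plans a 95% interval for the responder proportion. At 1/10 the score interval runs from 1.8% to 40%, so a reader would see that 10% is not excluded. This helps, but the interval is listed as secondary and tied to no conclusion.

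Fourth, the trial seeks safety and potential efficacy, and the article states no rule for declaring success. So one may say that the test is significant, but not that the plan would declare the treatment effective.

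A reader might also infer that a treatment short of 10% would usually be significant at n = 10. That holds only for true rates above about 6.7%, where 1 − (1−p)^10 reaches 50%; at 5% the chance is 40%.

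**Conclusion.** The concern holds in this form: the primary test, as printed, is significant with a single improved patient at every planned size from 6 to 20, including results (1/10, 1/20) that do not exceed the 10% the protocol links to benefit. This rests on the printed 0.1% and a conventional 0.05 level, and holds one- or two-sided and by Z-test or exact test. The false-positive figures (10%, 18% or 40% at n = 10) rest on assumed untreated rates of 1%, 2% or 5%. Given the open-label, single-arm design with continued rehabilitation, rejecting 0.1% is not evidence of efficacy. Whether 0.1% is a slip for 0.1 (10%) cannot be settled from the article; it is a question for the sponsor.

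**What to change.** In Statistical Analysis, Primary Outcome Measure:

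1. Confirm whether 0.1% was meant as 0.1, that is 10%, and correct it if so.
2. If 0.1% is kept, state that rejecting it shows only that at least one patient improved. Conclude that the Sample Size benefit criterion is met only if the exact (Clopper-Pearson) 95% lower limit exceeds 10%: at least 3/6, 4/10 or 6/20. Do not use the planned score interval for this rule.

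The change is to wording in the protocol and the analysis plan, with the ethics board and PMDA approval that the protocol requires for amendments. No extra patients are needed. The cost is a higher hurdle for claiming benefit: at n = 10 a true rate of 30% would meet it only 35% of the time, and at n = 6 only 26%. Replacing the null by 10% when 0.1% was intended would be a redesign, with the minimum of 6 to be derived again; this fix does not ask for that.

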**Methods:**

The (phase 2) trial will be a single-arm, open-label trial with the primary objective of confirming the safety and efficacy of autoserum-expanded autologous MSCs (STR-01; produced under good manufacturing practices) when administered to patients with chronic brain injury. The estimated number of enrolled participants is 6 to 20 patients with a modified Rankin Scale grade of 3 to 5. The assessment of safety and the proportion of cases in which the modified Rankin Scale grade improves by 1 point or more at 180 days after the injection of STR-01 will be performed after MSC infusion.

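### The primary Z-test with continuity correction cannot give a correct p-value against a 0.1% null with 6 to 20 patients; an exact binomial test should replace it

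*Protocol article*

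**What the plan says.** The protocol article, Statistical Analysis, Primary Outcome Measure, fixes both the null and the test. On the null: "We assume that the proportion of cases without MSC infusion in which the mRS grade improves by 1 point or more will be 0.1" percent. On the test: "We will perform a Z-test with continuity correction at 180 (±14) days after MSC infusion".

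The Sample Size section relies on the same test. It names a benchmark of clinical benefit, "if the proportion of cases in which the mRS grade improves by 1 point or more exceeds 10" percent, and concludes that "a minimum of 6 people is required". It first gives the numbers as "We will recruit 10 people (minimum: 6; maximum: 20) with a modified Rankin Scale (mRS) grade of 3 to 5" and then says the target "was determined to be 10 (minimum: 6; maximum: 10), under the consideration of dropout". The abstract has "The estimated number of enrolled participants is 6 to 20 patients".

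Under Secondary Outcome Measure, the same proportion is to be estimated with "the 95% CI by using the scoring method". The article states no alpha, sidedness or power, and does not say whether the Z statistic uses the null variance or the variance estimated from the data.

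**The concern.** A Z-test for a proportion needs several expected events under the null. Here far less than one is expected: the null distribution of the responder count is almost entirely at zero, and its skewed tail looks nothing like a normal tail. A continuity correction shifts the statistic by half a patient but does not change that shape.

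The primary p-value is the number that readers will take from this trial, and the Discussion says that the data will feed the design of larger trials. A p-value of the order of 1e-10 from one improved patient in six would mislead that decision. If the other variance were used, the same patient would give a p-value near 0.3. One named test would then support opposite conclusions on the same data.

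**Working it through.** **Inputs.** p0 = 0.001 (Primary Outcome Measure). n = 6, 10 and 20 (Sample Size, abstract). One sentence in Sample Size gives 10 as the maximum; on that reading the n = 20 figures drop out. Alpha, sidedness and power are not stated, so the levels below are assumptions.

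**The plan's own figure, n = 6.** Take the one-sample formula n = ((zα√(p0q0) + zβ√(p1q1))/(p1 − p0))², then the correction n/4 × (1 + √(1 + 2/(n·d)))² with d = p1 − p0. Use p1 = 0.10, which the article calls a threshold of benefit and not a design alternative.
- 80% power, two-sided 0.05: (1.96 × 0.0316 + 0.842 × 0.3)/0.099 = 3.18, squared 10.09, corrected 18.8, so 19.
- 80% power, one-sided 0.05: 18.15, so 19.
- 90% power: 30 (two-sided) or 29 (one-sided).
- 50% power: 6.67 (two-sided 0.05), 6.38 (one-sided 0.05) or 6.06 (one-sided 0.10), so 7 in each case.

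The 6 is not reproduced. Because alpha, power and the alternative are missing, it can be neither confirmed nor refuted.

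**Expected responders under the null.** 6 × 0.001 = 0.006; 10 × 0.001 = 0.01; 20 × 0.001 = 0.02.

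**One responder, null variance.** z = (x − n·p0 − 0.5)/√(n·p0·q0). The exact one-sided value is P(X ≥ 1) = 1 − 0.999ⁿ.

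| n | z | one-sided p, Z-test | exact p | exact ÷ Z |
|---|---|---|---|---|
| 6 | 0.494/0.0774 = 6.38 | 8.8e-11 | 0.0060 | 6.8e7 |
| 10 | 0.490/0.0999 = 4.90 | 4.7e-7 | 0.0100 | 2.1e4 |
| 20 | 0.480/0.1414 = 3.40 | 3.4e-4 | 0.0198 | 58 |

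A two-sided Z p-value halves the last column (3.4e7, 1.1e4, 29).

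**One responder, estimated variance.** z = (p̂ − p0 − 1/(2n))/√(p̂(1 − p̂)/n).

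| n | z | one-sided p, Z-test | Z ÷ exact | responders needed at two-sided 0.05 |
|---|---|---|---|---|
| 6 | 0.0823/0.1521 = 0.54 | 0.294 | about 49 | 3 (p = 0.042) |
| 10 | 0.0490/0.0949 = 0.52 | 0.303 | about 30 | 4 (p = 0.024) |
| 20 | 0.0240/0.0487 = 0.49 | 0.311 | about 16 | 5 (p = 0.021) |

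In this version 1 of 10 is not significant, although the score interval planned for the same data (taken as Wilson: 1.8% to 40.4%) excludes 0.1%.

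**No responders.** Both tests are non-significant. At a true rate of 10% this has probability 0.9⁶ = 53%, 0.9¹⁰ = 35% and 0.9²⁰ = 12%.

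**Decision.** With the null variance, checking every possible count for n = 6 to 20, the Z-test and the exact test reject in the same cases at one-sided 0.025 and 0.05: one or more responders. That rule has type I error 0.60%, 1.00% and 1.98% at n = 6, 10 and 20, and power at a true 10% of 46.9%, 65.1% and 87.8%. With the estimated variance at n = 6, three responders are needed, and power at a true 10% falls from 46.9% to P(X ≥ 3) = 1.6%.

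**The case against.** The strongest reply is that nothing the trial would conclude depends on this. With the null variance, the Z-test and the exact test give the same verdict for every possible result, and the false-positive rate stays at or below 2.0%. That stands, and it limits the point: a reader might infer that the planned test inflates the type I error, and under the stated null it does not. The reply does not rescue the reported p-value, and it lapses if the estimated variance is used.

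A reader might also infer that the decision changes because, against a 10% null, the Z-test can reject where the exact test does not; 3 of 8 gives z = 2.00 against an exact p of 0.038. The article does not test against 10%. Even if it did, the two tests would disagree at one-sided 0.025 only for 3/7, 3/8, 4/12, 4/13, 5/18 and 5/19, and at one-sided 0.05 only for 3/9 and 4/15. They never disagree at n = 6, 10 or 20.

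The score interval may look equally suspect, since its coverage can drop to 83 to 84%. That drop occurs only at true rates near 1 to 3%. Averaged over all true rates its coverage is 95.3% to 95.5% for these sample sizes, against 97.7% to 98.9% for the exact interval. Preferring one over the other is a trade-off, and the planned interval is acceptable.

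Finally, details are deferred to an analysis plan that is not shown. That plan may settle the variance and alpha. It cannot make the Z-test suitable, and an exact test there would contradict the article.

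**Conclusion.** The point holds in a limited form. The article names a test whose approximation fails at an expected null count of 0.006 to 0.02. Given at least one responder, the primary p-value is wrong, but the direction depends on a choice that the article leaves open. With one responder it is too small by a factor of 58 (n = 20) to 6.8e7 (n = 6) one-sided with the null variance, and too large by a factor of about 16 to 49 with the estimated variance. In the first case the decision is unaffected and the harm is a falsely extreme p-value. In the second, the rejection threshold rises from 1 responder to 3, 4 or 5, and real effects would be missed. If 10 is the true maximum, the one-sided error with the null variance and one responder is at least 2.1e4-fold.

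These figures assume p0 = 0.1% and the usual half-patient correction; the thresholds of 3, 4 and 5 also assume two-sided 0.05.

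A more serious weakness lies outside this point. Against a 0.1% null, one responder is significant under the exact test too. If the true untreated rate were 1%, the same rule would reject in 5.9%, 9.6% and 18.2% of trials at n = 6, 10 and 20; at 5%, in 26%, 40% and 64%.

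**What to change.** In Primary Outcome Measure, replace the Z-test by a one-sided exact binomial test and state alpha. Use 0.025 if the test is to agree with a two-sided 95% interval. This also removes the ambiguity about the variance.

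In Sample Size, drop the Z-test as the basis for the minimum of 6 and give the exact operating characteristics: alpha, the alternative, and power for the rule actually used. For rejection with one or more responders, power at 10% is 46.9%, 65.1% and 87.8% at n = 6, 10 and 20.

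The score interval may stay. An exact interval is optional, for consistency with the test: for 1 of 10 it runs from 0.25% to 44.5%, against 1.8% to 40.4%.

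The cost is wording: no extra patients, visits or data. The downside is that p-values will be larger and less impressive than under the null-variance Z-test. The choice of the 0.1% null needs its own justification; this change does not supply it.
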